## Abstract

**Background:**

Quadratus lumborum block (QLB) is increasingly gaining popularity as a novel abdominal truncal block in abdominal surgery; however, the mechanism of QLB is not yet thoroughly illustrated. The focus of our study is transmuscular QLB (TMQLB), as the latest anatomical evidence shows that anesthetics spread into the thoracic paravertebral space to exert an analgesic effect. Therefore, we designed this study to compare TMQLB with thoracic paravertebral block (TPVB) in laparoscopic renal surgery in the hope of providing clinical evidence on the analgesic mechanism of TMQLB and its application in laparoscopic renal surgery.

**Methods:**

This trial is a prospective, randomized, single-center, open-label, parallel, three-arm, non-inferiority trial. We intend to include 120 participants undergoing laparoscopic nephrectomy and before surgery they will be randomized into three groups for postoperative pain control: TMQLB experimental group 1 (0.4 ml/kg body weight 0.5% ropivacaine), TMQLB experimental group 2 (0.6 ml/kg body weight 0.5% ropivacaine) or TPVB control group (0.4 ml/kg body weight 0.5% ropivacaine at vertebra T10). Patients will be excluded if they have allergy to anesthetics, infection at the injection site, are on coagulopathy or anticoagulants, on analgesics for chronic illness, have history of substance abuse or have a barrier to communication. Morphine is given in boluses of 1.5~2 mg by intravenous patient-controlled analgesia (IPCA) in the first 48 h after surgery. The primary outcome is the difference between TMQLB group 1 and the TPVB group in the mean visual analogue scale (VAS) pain score in the first 24 h after surgery. Secondary outcomes are the difference between TMQLB group 2 and the TPVB group in the mean VAS score in the first 24 h after surgery, cumulative morphine consumption, long-term pain control, dermatomal distribution of sensory loss, nausea score, pruritus score, ambulation time, time till recovery of bowel movement, quality of recovery, postoperative length of hospital stay and patient satisfaction with anesthesia. Safety data on procedure-related complications will also be summarized.

**Discussion:**

This will the first randomized controlled trial to compare TMQLB with TPVB for analgesia in laparoscopic surgery. This trial aims to provide important clinical evidence to elaborate on the analgesic mechanism of TMQLB.

**Trial registration:**

ClinicalTrials.gov, NCT03414281. Registered on 9 January 2018.

**Electronic supplementary material:**

The online version of this article (10.1186/s13063-019-3359-7) contains supplementary material, which is available to authorized users.

## Strengths and limitations of this study

This will the first randomized controlled trial to compare transmuscular quadratus lumborum block with thoracic paravertebral block for analgesia in laparoscopic surgeryThis trial will provide important clinical evidence to elaborate the analgesic mechanism of transmuscular quadratus lumborum blockThe methodology of this trial has strengths that include a well-designed intervention, computerized randomization, blinded assessment and data-analysis and appropriate estimation of the sample sizeThe relatively small sample size may not be adequate to detect a difference in safety difference between the two block techniques

## Background

Quadratus lumborum block (QLB) is a novel abdominal truncal block providing analgesia for abdominal surgery including cesarean section, laparoscopy, colostomy, pyeloplasty and hernia repair [1–5]. Currently, there are four different approaches for QLB, with local anesthetic injected around the quadratus lumborum (QL) muscle from various directions. The QLB 1 was first proposed by Blanco in 2007: the needle is inserted into the plane between the psoas major muscle and the QL muscle and the local anesthetic is injected into the anterolateral margin of the QL muscle, which is also known as the lateral QLB [6]. The QLB 2 approach involves injection of the anesthetic posterolateral to the QL muscle [7], and so QLB 2 is also referred to as posterior QLB. Later, Børglum et al. [8] described another approach, transmuscular QLB (TMQLB), whereby the needle is advanced through the latissimus dorsi and the QL muscle in a posterior-anterior direction with the injection performed anterior to the QL muscle. This approach is also referred to as QLB 3 or anterior QLB. Last but not least, there is intramuscular QLB, whereby the anesthetic is injected directly into the QL muscle [5].

When first proposed by Børglum, TMQLB was designed to alleviate pain in intraperitoneal and retroperitoneal surgical procedures. The original hypothesis of the analgesic mechanism of TMQLB was that the injectate deposited within the plane between the QL and psoas major muscle would spread cranially to the thoracic paravertebral space to exert its analgesic effect. But it is not until recently that solid anatomical findings have verified this assumption. Børglum et al. [9] conducted a cadaver study investigating the spread of dye solution after TMQLB and showed convincingly that the injectate could reach the thoracic sympathetic trunk and the ventral rami of the lower thoracic (T9–T12) spinal nerves in the thoracic paravertebral space. The injectate spread cranially from the point of lumbar administration between the QL muscle and the psoas major muscle to reach the paravertebral space via a pathway posterior to the medial and lateral arcuate ligaments.

Based on this anatomical evidence, we could assume that the analgesic effect of TMQLB will be comparable to thoracic paravertebral block (TPVB) because both approaches exert analgesic effects by infiltrating the thoracic somatic and sympathetic nerves in the thoracic paravertebral space. Despite infrequent complications with TPVB, concerns remain about the possibility of pneumothorax, vascular or dural puncture and epidural or intrathecal spread. Moreover, as a deep block performed in a non-compressible space, TPVB involves a risk of bleeding in the thoracic paravertebral space, which is difficult to deal with and clotting is dependent on the patient’s hemostasis [10]. TPVB is thus relatively contraindicated in patients on anticoagulation medication as suggested by the anticoagulation guidelines of American Society of Regional Anesthesia and Pain Medicine (ASRA) [18]. By contrast, the risk of injury associated with TMQLB is lower because the passage of the needle and the endpoint is within muscle and the fascial plane, distant from the peritoneal cavity, abdominal organs, large blood vessels and nerves. Henceforth, if clinical evidence demonstrates that TMQLB provides similar analgesic effect to TPVB, the complications associated with TPVB could be avoided with the application of TMQLB. However, it is regrettable that high-quality randomized clinical trials (RCTs) on the efficacy and safety of TMQLB in abdominal and retroperitoneal surgery are scarce and there has been no direct comparison between TMQLB and TPVB in these scenarios.

### Objectives

The aim of this study is to design a prospective RCT to compare TMQLB with TPVB in terms of the efficacy of analgesia and the quality of recovery in laparoscopic renal surgery. Our hypothesis is the analgesic efficacy of TMQLB in laparoscopic renal surgery is non-inferior to that of TPVB.

## Methods

### Study design

Our trial is a prospective, randomized, single-center, open-label, parallel, 3-arm, non-inferiority trial, the objective of which is to evaluate pain relief and the quality of recovery in laparoscopic renal surgery using TMQLB compared with TPVB. The overall trial scheme is illustrated in Fig. 1 (see Additional file 1 for the SPIRIT Checklist). Institutional research ethics board approval was obtained from Peking Union Medical College Hospital (PUMCH). The trial will be conducted at PUMCH in accordance with the International Conference on Harmonisation (ICH) guideline for Good Clinical Practice (GCP). Full written informed consent will be obtained from each participant by a qualified member of the research team before the intervention. This trial was registered with the US National Institutes of Health Clinical Trials registry (NCT03414281). Participants will be randomized into three groups receiving TMQLB (two dosing groups) or TPVB for postoperative pain control.

**Fig. 1 Fig1:**
[figure not shown]
Flow diagram of the study. TMQLB, transmuscular quadratus lumborum block; TPVB, thoracic paravertebral block; VAS, visual analogue score; QoR, quality of recovery

### Eligibility criteria

#### Inclusion criteria

Participants enrolled in this trial will be:17~80 years of ageCategorized as American Society of Anesthesiologists (ASA) class I–IIIUndergoing laparoscopic nephrectomy

#### Exclusion criteria

Patients will be excluded if they:Have known allergy to the anesthetics being usedHave infection at injection siteAre receiving coagulopathy or have history of anticoagulant useAre taking analgesics for chronic illness or have history of substance abuseAre unable to appropriately describe to the investigators their postoperative pain or recovery (e.g., language barrier or neuropsychiatric disorder)

### Interventions

Intravenous access and standard ASA monitoring will be established after patients arrive at the preoperative holding area. Premedication with 1–2 mg midazolam will be considered depending on the patient’s condition. All patients will receive ultrasound-guided block administered by the same experienced attending anesthesiologist. After the block, the anesthesia induction regimen will be as follows: propofol (2 mg/kg body weight), fentanyl (1 μg/kg body weight), and rocuronium (0.9 mg/kg body weight). Patients will be intubated endotracheally. During the surgery, sevoflurane and a mixture of O_2_/N_2_O will be used for maintenance to keep the bispectral index (BIS) within the range of 40–60. Fentanyl will be administered as needed to control the heart rate and blood pressure to within ± 20% of the baseline values.

#### TMQLB experimental group 1

For participants in the TMQLB group 1, the QLB will be performed using the transmuscular approach. The patient is placed in the lateral position. The patient is scanned using the curved (C1–5) probe of the Philip CX50 Ultrasound Scanner is used and is located vertical to the iliac crest at the posterior axillary line to find the Shamrock sign. The 22-G needle is then inserted in plane and directed to the QL muscle. After the proper position of the needle tip between the psoas major muscle and the QL muscle is confirmed, ropivacaine 0.5% at 0. 4 ml/kg body weight with adrenaline at a ratio of 1:200,000 is injected into the interfascial plane. The effective block is confirmed by the sign of local anesthetic spreading around the QL muscle and the loss of sensory function in the area. If there is no block of sensory function after 45–60 min, then it is defined as an unsuccessful block. All interventions will be performed by the same experienced attending anesthesiologist.

#### TMQLB experimental group 2

The intervention in TMQLB group 2 conforms to that used in TMQLB group 1 except that the dose of ropivacaine is 0. 6 ml/kg body weight.

#### TPVB control group

In the TPVB group, the patient is placed in the lateral position, the spinous processes of vertebra T10 are identified and marks are made 2 cm lateral to the spinous processes. The linear (L12–3) probe of the Philips CX50 is placed transversely at the mark to identify the paravertebral space. Then a 22-G needle is inserted in-plane in a lateral to medial direction and advanced until the tip reaches the paravertebral space surrounded by the parietal pleura and the superior costotransverse ligament. Then, ropivacaine 0.5% at 0.4 ml/kg body weight with adrenaline at a ratio of 1:200,000 is injected into the paravertebral space of vertebra T10. The block is confirmed as correct by the sign of the parietal pleura being pressed down by the local anesthetic. A successful block is defined as loss of sensory function in the area.

#### Postoperative analgesia

Each participant will receive standard postoperative intravenous patient-controlled analgesia (IPCA) at the end of surgery. Morphine is given in boluses of 1.5–2 mg as needed without baseline infusion in the first 48 h postoperatively, with a lockout time of 10 min. The 1-h limit is 6–8 mg morphine.

### Randomization and allocation concealment

All eligible patients will be randomized to TMQLB group 1, TMQLB group 2 or the TPVB group in a ratio of 1:1:1, using the computerized SPSS package (version 22; SPSS Inc., Chicago, IL, USA). The randomization sequence will be computer-generated by a professional statistician who is not involved in the implementation and statistical analysis of the study. Allocation concealment will be ensured by using sealed, opaque, sequentially numbered envelopes. These assignment envelopes will only be opened after the inclusion of the patient in the study. A study coordinator will be responsible for enrolling patients, obtaining informed consent and requesting randomization.

### Blinding

Because of the nature of the intervention, the anesthesiologist who performs the intervention and the trial participants cannot be blinded to the allocation of the intervention. Therefore, this is an open-label study whereby the investigator and patients are not blinded. However, the outcome assessor and statistician who performs the data analysis are blinded to the allocated intervention. The participant’s allocated intervention will not be revealed until the final data analysis is completed.

### Outcomes

#### Primary outcome

The primary outcome of this trial is mean visual analogue scale (VAS) score for pain in the first postoperative 24 h, between TMQLB group 1 and the TPVB group. The VAS score will be recorded at 0, 2, 4, 8, 12 and 24 h after surgery, and the primary outcome will be calculated as the mean VAS scores measured at these time points. The VAS is an internationally recognized scale for assessment of pain on an 11-point scale ranging from 0 to 10 points, with 0 defined as no pain and 10 defined as the worst pain imaginable.

#### Secondary outcomes

Secondary outcomes are as follows:Mean VAS score in the first postoperative 24 h between TMQLB group 2 and the TPVB group. In theory, the dose of local anesthetic in TMQLB group 1 is lower than that in TMQLB group 2, hence, if group 1 satisfies the non-inferiority hypothesis, the mean VAS score in group 2 should also be non-inferior to that in the TPVB group. If not, the results of the comparison between TMQLB group 2 and the control will be hypothesis-generating.Cumulative morphine consumption, which will be registered at 0, 2, 4, 8, 12, 24, 48 and at 72 h and 7 days after surgery, and will be calculated as the sum of the values.Long-term pain control, which will be evaluated by VAS at 48 and 72 h and at 7 days after surgery.Dermatomal distribution of sensory loss, which will be evaluated at 10, 20, 30 and 40 min after the intervention by pinprick test using Von Frey filaments.Nausea score, which will be recorded at 0, 2, 4, 8, 12, 24 and 48 h after surgery.Pruritus score, which will be recorded at 0, 2, 4, 8, 12, 24 and 48 h after surgery.Ambulation timeTime of recovery of bowel movement (defined as the time to first flatus).Quality of recovery evaluated by the self-assessment quality of recovery (QoR) scale at 3 days and 5 days after surgery. The QoR is a 15-item questionnaire, scored on a scale of 0–10 pertaining to the patient’s comfort, support system, pain, wellbeing and ability to carry out daily activities, where 0 indicates none of the time and 10 indicates all of the time [11].Length of postoperative of hospital stay.Patient satisfaction with anesthesia evaluated using the Chinese version of the Bauer questionnaire at 48 h after surgery [12].

### Trial safety

The ultrasound-guided block will be performed only after intravenous access and standard monitoring is established for the patient. The intervention will be stopped if any adverse event occurs during the procedure. After the intervention, research personnel will continue monitoring the patient to detect any possible adverse events until the patient enters the operating room. Monitoring will continue in the postanesthesia care unit (PACU) and the surgical ward. Research personnel will follow up the patient at 0, 2, 4, 8, 12, 24, 48 and 72 h and at 7 days after surgery. All adverse events recorded in this period will be reported to the adverse event registration system of the hospital.

### Data collection and management

Baseline data will be collected, including age, gender, weight, body mass index (BMI), ASA grading, duration of surgery and vital signs. We will also document intervention-related complications including hematoma, organ injuries, and lower extremity weakness in TMQLB, and vascular puncture, pleural puncture, pneumothorax and dural puncture in TPVB. All personal information will be registered in an environment limited to medical personnel to maintain absolute confidentiality.

A web-based electronic data capture (EDC) system will be built for data collection. During the follow-up period, the outcome assessor will record the data on standardized paper case report forms (CRFs) to ensure all data points are noted. After the paper CRF is completed for each patient, it will be entered into the electronic CRF and saved in the trial database. The database is protected by password, but still allows for data audits to check completeness and accuracy. Data lockup will be implemented on completion of the study and the researchers will not be able to modify the data. The allocation will be blinded until all data analyses are completed. The paper CRFs and the electronic database will be preserved for at least 5 years after publication in case of any inquiry.

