## Discussion

Although QLB is gaining popularity as analgesia in abdominal surgery, there has been limited clinical study of its clinical efficacy compared with other truncal block techniques. Most of the current studies concentrate on the comparison of QLB with other abdominal blocks, especially the transversus abdominis plane (TAP) block, because QLB was originally proposed as a different form of TAP [4, 5, 15, 16]. Also, the analgesic mechanism of TMQLB is still controversial. The anatomical work performed by Børglum et al. [9] reveals that in TMQLB the injectate spreads cephalad to the thoracic paravertebral space. This convincing study prompted us to speculate that TMQLB may have a similar analgesic profile to TPVB, which is essentially a thoracic truncal block, and this inspired us to conduct a trial to compare these two block techniques and further validate the theory from a clinical aspect.

The expected results will provide clinical evidence to verify the analgesic mechanism of TMQLB put forward by Børglum and promote its application in intraperitoneal and retroperitoneal surgery. Furthermore, if the efficiency of TMQLB is equal to that of TPVB, TMQLB could replace TPVB in abdominal surgery because it is relatively safe and convenient to perform, while TPVB implicates a possibility of pneumothorax, dural puncture and hematoma in the thoracic paravertebral space [10, 14].

As the mechanism of the injectate of TMQLB reaching the paravertebral space is primarily by spreading via the pathway posterior to the arcuate ligaments, it could be assumed that the amount of the injectate will consequently determine the extent to which the thoracic nerves are blocked. Henceforth, we designed three intervention groups with two dosing groups for TMQLB to explore whether the amount of injectate would improve the coverage and analgesic effect. This may also provide a clue to the appropriate dosage for anesthetics in TMQLB.

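### Block complications are listed separately by technique with no shared item, so ascertainment may be unequal in the safety summary that supports replacing TPVB with TMQLB

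*Protocol article*

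**What the plan says.** The Data collection and management section assigns complications to techniques. It says that the team will document "intervention-related complications including hematoma, organ injuries, and lower extremity weakness in TMQLB, and vascular puncture, pleural puncture, pneumothorax and dural puncture in TPVB".

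The case for the new block is comparative. On TPVB, the Background says that "concerns remain about the possibility of pneumothorax, vascular or dural puncture and epidural or intrathecal spread" and adds that "TPVB involves a risk of bleeding in the thoracic paravertebral space". It then states: "By contrast, the risk of injury associated with TMQLB is lower". The Discussion repeats the argument for replacement, saying that "TPVB implicates a possibility of pneumothorax, dural puncture and hematoma in the thoracic paravertebral space".

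Three other statements bear on the point:
- The Trial safety section has research personnel watch every patient for any adverse event, before surgery and then at fixed visits to 7 days, without distinction by arm.
- The Abstract promises only a summary of procedure-related complications.
- The Blinding section says that "the outcome assessor and statistician who performs the data analysis are blinded to the allocated intervention", and Data collection and management has that assessor complete standardized case report forms during follow-up.

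**The concern.** A complication that staff are told to look for is usually found more often than one left to spontaneous report. If hematoma is prompted after TMQLB and not after TPVB, and vascular puncture the other way round, the summary table partly reflects where people were asked to look.

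This matters because safety is the reason for accepting a block whose analgesia is only non-inferior. The Background and Discussion argue that TMQLB could take the place of TPVB because its harms are fewer or milder, and the Discussion includes safety in the purpose of the study. Readers will compare the arms on complications whether or not a test is planned.

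There is a possible second effect. If the technique-specific items stand on the form that the blinded assessor completes, the form itself could disclose the allocation.

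**Working it through.** The document gives no complication rate and no figure for this point, so the main check sets the sections side by side.

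| Complication | Named as a TPVB risk in Background or Discussion | Listed for TMQLB | Listed for TPVB |
|---|---|---|---|
| Bleeding or hematoma | Yes, both | Yes (hematoma) | No |
| Vascular puncture | Yes, Background | No | Yes |
| Dural puncture | Yes, both | No | Yes |
| Pneumothorax | Yes, both | No | Yes |
| Pleural puncture | No | No | Yes |
| Epidural or intrathecal spread | Yes, Background | No | No |
| Organ injury | No | Yes | No |
| Lower extremity weakness | No | Yes | No |

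Seven complications are named in the two lists (3 + 4), and none is in both. The hematoma row is the clearest conflict: the article argues this harm against TPVB and then lists it for TMQLB.

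**Direction of the possible bias.** Let r be the true rate of a complication and s the probability that an event is recorded. The expected recorded proportion is r × s. If the true rate is the same in both techniques, the expected recorded difference (TPVB minus TMQLB) is r × (s_TPVB − s_TMQLB).
- For hematoma, prompting favours s_TMQLB > s_TPVB, which makes TMQLB look worse.
- For vascular puncture, dural puncture and pneumothorax the inequality reverses, which makes TPVB look worse.
- The size is unknown. It is zero if open-ended monitoring works as well as prompting, and at most r if unprompted events are never recorded.

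**How much one event counts.** Arms are 40 each (36 / 0.9 = 40 after the 10% dropout allowance), so 80 patients receive TMQLB.
- One event is 1/40 = 2.5 percentage points in a single arm, or 1/80 = 1.25 points with the TMQLB arms combined.
- As a yardstick only, since no test is planned: with no events in 80 TMQLB patients, Fisher's exact test (two-sided 0.05) first reaches significance at 3/40 under TPVB (p = 0.035). One event more or fewer changes that result.

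**Precision, which the lists do not affect.** With zero events the one-sided 95% upper limit is 1 − 0.05^(1/n): 7.2% for n = 40 and 3.7% for n = 80. These limits come from the arm sizes and would be the same with a common list.

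**The case against.** The strongest reply is that no arm-specific form is described. The lists are introduced as examples, the case report forms are called standardized, and the forms themselves are not shown, as is normal for an article. The Trial safety section would count a hematoma after TPVB, or a vascular puncture during TMQLB, as an adverse event to be recorded. Safety is not among the secondary outcomes, it is only to be summarized, and the strengths and limitations list already admits that the sample may be too small to show a safety difference.

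Most of this stands, and it limits the point. A reader might infer that the arms use different checklists, that none of the seven complications can be compared, or that every difference will be produced by the form. The document supports none of these: the lists are not exhaustive, and monitoring of any adverse event is common to all patients.

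What the reply does not remove is the assignment of named items by technique. Condensing a protocol explains missing detail; it does not explain placing hematoma under TMQLB while arguing it as a TPVB hazard. Open-ended reporting to a hospital system is also not equivalent to a solicited item. The admission about sample size concerns precision, not bias.

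The blinding argument is conditional. The article does not say who records procedural events such as punctures, and it ties the assessor's form to the follow-up period.

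**Conclusion.** The point holds as a risk of unequal ascertainment. The technique-specific lists share no item, they contradict the Background and Discussion on bleeding and hematoma, and they leave out epidural or intrathecal spread, which the Background raises. Followed as written, they prompt for a given harm in one technique and not in the other, which may bias the safety summary either way. The magnitude cannot be derived from the document; the conclusion assumes that prompted events are recorded more completely than unprompted ones. At 40 per arm, a difference of one or two recorded events could shape the reading of the table.

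It does not follow that the trial is unable to compare safety, or that the assessor will be unblinded. The primary pain analysis and the sample size are not affected by the lists themselves.

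**What to change.** - Replace the two lists with one common yes/no list for all three arms: bleeding or hematoma, vascular puncture, organ injury, pleural puncture, pneumothorax, dural puncture, epidural or intrathecal spread, lower extremity weakness.
- Solicit every item in the same way and at the same visits in each arm, alongside the existing open-ended adverse event monitoring.
- Have the operator, who is unblinded in any case, record the procedural items, so that the assessor's form carries nothing specific to a technique.
- Tabulate each item by arm with exact confidence intervals.

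The cost is one page of the case report form, with no new visit or procedure and no change in sample size. The Trial status section says recruitment was already under way at submission, so data on the added items may be incomplete for patients enrolled before the change; the report should say how many. The safety comparison will remain imprecise at these arm sizes, but it will no longer depend on which items were prompted in which arm.
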